#### Independent variables collection

For both clinical trials described, available data will be collected from a data repository (dental records) administered by the researchers. Variables as time since the last consultation, oral health conditions associated (previous needs, caries experience, treatment adhesion/retention, oral-related habits, socioeconomic factors) may be used as independent variables. In addition, other independent variables will be collected parallel to intervention (teleconsultation), as changes in habits during the pandemic, level of education, age and occupation of the caregiver users involved in teleservice and previous experiences in health assisted by technologies.

#### Statistical methods

We will adopt the intention to treat analysis for both clinical trials, and all recruited participants will be considered when expressing our findings. Imputations of the outcomes will be considered whenever missing data is detected. In these cases, using conditional imputation methods will be used.

##### Before-and-after study

Firstly, we will calculate the problem-solving rate achieved with non-face-to-face care. Besides, a subgroup analysis will consider different demands identified. We will also calculate the average time of resolution of the demands (difference between the moment of the appearance of the complaint or demand and the moment of its resolution) and the reduction of the waiting time (time-lapse from when the care is provided and the regular face-to-face activities re-opening).

Regarding children's and caregivers' perception, we will calculate the usability rate (ease of use reported by caregiver users), satisfaction with the tools, behavior towards proposed strategies, and difficulties encountered, dividing them into difficulties with technologies and not related to technologies. Regression models will demonstrate the association of demand solving and the independent variables mentioned above. The same statistical approach will be used to outcomes related to the children's and caregivers' perception (usability, satisfaction, and behaviour to the technologies with the resolution of cases) and the time to resolution of complaints will be considered a dependent variable of conditional risk models. The events will be attention needs and the time counted from the last face-to-face contact. In these models, we will explore as independent variables the other variables also mentioned above, as well as aspects related to the difficulties reported by users.

The qualitative content analysis of the non-face-to-face consultations mediated by technology will be descriptive. It will look for possible explanations to different caregivers' perceptions and identify barriers and facilitators associated with the type of care offered.

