#### Outcomes

As the primary outcome for this before-and-after study, we consider problem-solving, considering the participant as the measurement unit. We will consider all the complaints pointed out by patients and their families during the baseline consultation. To measure that, a 2-weeks-later interview using the same platform (V4H) will address aspects relevant to understanding if the patients' and families' demands are solved during this time. A checklist to identify possible barriers and facilitators related to each type of complaint will be employed on these interviews. The time to resolution of the complaint will be computed as a secondary outcome.

Children will also be asked to toothbrush and floss during this assessment consultation. An external assessor will check the problem-solving related to the demand for oral hygiene orientations. The guidelines for orientation will be used as the reference standard to check if the demand was solved. If the child fulfils all oriented aspects, the demand is fully solved. If at least one assessment criterion is fulfilled, it is considered a partially solved demand. Cases of non-compliance with intervention sessions or those families that give up the consultations were also considered to understand the studied service's implementation.

Other outcomes will be assessed as secondary ones. The teleservice platform will measure consultation time. Technological and non-technological difficulties during the consultation (absences or delays, non-compliance, difficulties in using the platform, accessing the internet or even the computer or mobile phone) will be registered by an external assessor in a specific file at the end of the online session. The caregivers' and child's perceptions on the use of technologies in primary dental care will be collected by specific questionnaire [21] in the two-week-later assessment.

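### If resolution is the event, the time-to-resolution model counts time from the last face-to-face contact and may include time since the last consultation, a part of that same time

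*Protocol article*

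**What the plan says.** All of this concerns the before-and-after study in the protocol article.

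- **Outcome.** The Outcomes section makes it secondary: "The time to resolution of the complaint will be computed as a secondary outcome".
- **Model.** Under Statistical methods, Before-and-after study, "the time to resolution of complaints will be considered a dependent variable of conditional risk models".
- **Event and clock.** The next sentence reads "The events will be attention needs and the time counted from the last face-to-face contact".
- **Covariates.** It continues: "In these models, we will explore as independent variables the other variables also mentioned above". The list it points back to, under Independent variables collection, opens with "Variables as time since the last consultation, oral health conditions associated". Those variables "may be used as independent variables", so they are allowed rather than fixed.
- **A second definition of resolution time.** Earlier in the same subsection the average time of resolution is the "difference between the moment of the appearance of the complaint or demand and the moment of its resolution".
- **When resolution is learned.** "a 2-weeks-later interview using the same platform (V4H) will address aspects relevant to understanding if the patients' and families' demands are solved".

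The text mentions neither delayed entry nor leaving out a covariate that overlaps with the clock.

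**The concern.** Face-to-face care at the unit was suspended (Study setting). For most children the last recorded consultation should therefore be the last face-to-face contact, which is where the model's clock starts. A demand still open at the teleconsultation has already used up the whole gap. If its event is resolution, the modelled time is the gap plus whatever follows, and the gap is also available as a predictor.

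The fitted model would then say that children left longer without care take longer to have their demands solved, even if resolution after the teleconsultation has nothing to do with the gap. In a study that wants an overview of what the interruption of care did (Trial design and participant timeline), such a coefficient could easily be taken for a finding. Other covariates correlated with the length of the gap could be distorted too.

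**Working it through.** **Structure.** Let G be the time from last face-to-face contact to teleconsultation, R the time from teleconsultation to resolution, and T the modelled time. For a demand open at the teleconsultation, T = G + R. If R is independent of G, then without censoring

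corr(T, G) = SD(G) / √(SD(G)² + SD(R)²).

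This is above zero whenever gaps differ between children.

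**Inputs.** The clock, dependent variable and covariate list come from the protocol. It gives no figure for this analysis and no distribution for G or R, so these are assumed. One assumed spread of G is 19 weeks, prompted by 750 children / 40 per week = 18.75 weeks (Study setting). That is throughput, not a measured gap distribution, so wider spreads were tried.

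**By hand.** G uniform over 19 weeks has SD 19/√12 = 5.49; over 52 weeks, 52/√12 = 15.01. R exponential has SD equal to its mean.

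- Spread 19, mean R 4 weeks: 5.49/√(30.1 + 16) = 0.81
- Spread 19, mean R 26 weeks: 5.49/√(30.1 + 676) = 0.21
- Spread 52, mean R 4 weeks: 15.01/√(225.3 + 16) = 0.97
- Spread 52, mean R 26 weeks: 15.01/√(225.3 + 676) = 0.50

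**Cox simulations with no true effect of G** (200 data sets per setting, 300 or 400 demands, R exponential and independent of G). The figures are the hazard ratio (HR) per month of G and the share of runs with p < 0.05.

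| Assumed setting | Clock from last contact | Clock from teleconsultation |
|---|---|---|
| Mean R 4 weeks; G = 50 weeks + 0–19 or 0–52 | 0.45, 100% | about 1.00, 2–8% |
| Mean R 26 weeks; same G | 0.83, 98–100% | about 1.00, 2–8% |
| Mean R 90 days, 180-day follow-up; G 360–540 days | 0.69, 100% | 1.00, 2.5% |
| Mean R 180 days, 365-day follow-up; G 360–540 days | 0.83, 100% | 1.01, 7.5% |
| Mean R 14 days, 14-day follow-up; G from 360 to 420, 540 or 720 days | 0.006–0.008, 100% | 1.00–1.01, 4.5–7.5% |

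A repeat of the first two rows gave 0.44 and 0.83 with 94–100% rejection, against about 1.00 and 1–7%. In the last row T is almost G itself (correlation 0.96–0.999), and the fitting routine gave convergence warnings. Those ratios show near-complete ordering by the gap and are not usable effect sizes.

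**Other readings of the same text.**

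- *Event is a need arising after last contact, censored at the teleconsultation.* G is then a censoring time, not a part of the event time: HR 0.99–1.00, rejection 5.5–8%. There is no artefact.
- *Clock from appearance of the complaint, complaints arising during the gap and resolving only after telecare.* The coupling is weaker but remains: HR 0.71–0.80, rejection 54–100%.
- *Last-contact clock with delayed entry at G, covariate kept.* HR 0.99–1.09, rejection 2.5–6%. This relies on the constant hazard that was simulated. At time t since last contact the hazard is h(t − G), which does not depend on G only if h is constant. If h falls with time since the teleconsultation, the ratio for G is pushed above 1; if it rises, below 1.

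**The case against.** A reader might infer that the plan commits to this model and that a false association is built in whatever the truth. The documents do not support that, for four reasons.

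1. The covariate is only permitted, for both clinical studies and for several models. An analyst could leave it out of this one, and final covariate choice and risk-set entry are often settled in an analysis plan not shown here.
2. The sentence that fixes the clock names attention needs as the event, not resolution. Read literally, with censoring at the teleconsultation, it produces no artefact.
3. The same subsection also defines resolution time from the appearance of the complaint.
4. Every hazard ratio above rests on assumed gaps and resolution times, ordinary Cox models stand in for what the protocol calls conditional risk models, and all simulated demands were open at the teleconsultation. The protocol expects some families to have sought care elsewhere.

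It can also be said that on a last-contact clock a longer gap truly does mean a longer total time, so the association misleads only when it is read as slower resolution under telecare.

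All of this stands as a limit on the claim, but it does not dispose of it. The sentence just before the clock names time to resolution as the dependent variable, so the need-arising reading discards the stated outcome. The complaint-appearance definition is given for an average, while the last-contact clock is given for the models, and moving to complaint appearance weakens the coupling without necessarily removing it. What is stated about event and origin is inconsistent, and completing a detail in an analysis plan does not cure that.

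**Conclusion.** The point holds conditionally. If resolution is the event, time runs from the last face-to-face contact, time since the last consultation is entered and no delayed entry is used, the outcome contains the covariate for demands open at the teleconsultation. A longer gap will then appear to slow resolution when it does not. In every setting tried, the hazard ratio per month was below 1 and rejection was about 94–100%. Only the direction and the near-certain rejection should be relied on; no particular hazard ratio can be attributed to this trial.

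What is certain from the text is narrower: the event, the last-contact clock and the complaint-appearance definition do not fit together, and nothing keeps the overlapping covariate out. The consequence is confined to an exploratory model of a secondary before-and-after outcome. The primary problem-solving rate and the RCT comparison are untouched. It deserves correction because the wording is cheap to repair and the artefact would be easy to mistake for a result.

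**What to change.** In Statistical methods, Before-and-after study:

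1. Name resolution of the complaint as the event of the time-to-resolution model. If time to a need arising is also wanted, state it as a separate model with its own origin and censoring.
2. For demands open at the teleconsultation, start the clock at the teleconsultation and keep time since the last consultation as a covariate. This is the safer choice, because it needs no assumption about how the hazard changes after the teleconsultation.
3. Alternatively, keep the last-contact clock and let each child enter the risk set only at the teleconsultation. In the runs above this restored valid testing without dropping the covariate, but with the covariate kept it relies on a roughly constant hazard after the teleconsultation, which should be checked.
4. Say that the complaint-appearance interval is for the descriptive average, so that the two definitions no longer compete.

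The cost is a few sentences. There is a real downside: the model then describes time from the teleconsultation only. Waiting before it, and demands resolved before it, must be reported descriptively, for instance through the complaint-appearance average already planned. Since resolution is learned at the two-week interview, that interview must record when each demand was resolved, which the secondary outcome needs in any case.

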##### The RCT (waiting list controlled)

This study will first compare the satisfaction with the health care received using the SERVQUAL score between the groups (with and without technology-mediated care). We will use an appropriate statistical test depending on the distribution of scores. The scores assigned for the perception of each dimension will also be compared. Appropriate regression analyses may also be performed to verify other variables' influence, besides the group (test vs control) on users' perception of the received care.

We will also compare the gaps (difference between expected and perceived) between groups. Comparisons between the perceived and the expected in each one of the groups will also be performed. Once again, distributions will be checked to choose the appropriate statistical approach to be used.

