#### Interventions

The family (including all children enrolled at the unit from the same family) will be randomized using stratified randomization by one researcher to one of the groups (intervention vs waiting list). The stratification will be performed considering the dentist will provide the non-face-to-face consultation and the week for inclusion. In this way, balanced randomization was obtained per professional each week.

Randomization order will be generated by the website sealedenvelope.com. The list will be stored under the supervision of the person responsible for randomization ([name]) and the principal investigator ([name]), in cloud storage and on a USB stick. The dentist who will provide the dental care will be unaware of randomization. They will receive the list with families/patients they are supposed to care for each week sent via email by the person in charge of randomization.

The two groups will differ according to the time of application of the intervention and outcome assessment. The non-face-to-face intervention group will receive the intervention immediately after randomization (t0). Then, after two weeks, the outcome will be measured as described further (t2). The waiting list group (control) will not receive the intervention at this time  and then assessed after the same period to permit controlling the answers (t2). Once this is done, the children on the waiting list will receive the intervention regularly (t3) and become part of the previously detailed list of before-and-after study participants. However, for the present RCT, only data without intervention will be considered (t2). The intervention will be provided as described in the before-and-after study *Interventions* section. Both groups will have been contacted by a research team member to explain the study and will have answered a baseline questionnaire previous to randomization (t-2). At this time, all participants will know the teleservice will be available, but they will not know when that will happen.

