#### Outcomes

We set the family's perception of dental care quality as the  primary outcome. We will consider the caregiver's perspective (those who participate in the non-face-to-face consultation) measured two weeks after the intervention (teleservice test group) or two weeks after waiting for care (control group) (Figs. 2, 3). The SERVQUAL questionnaire will be used [24] (Additional file 3). SERVQUAL is a summary instrument of multiple scales, with a high level of reliability and validity already used in Portuguese [24]. It can be used to understand users' expectations and perceptions concerning a wide range of services. In the present study, it is supposed the participants evaluate the degree to which they perceived the proposed service.

The questionnaire consists of 22 items, divided into 5 dimensions related to the service (tangible aspects—appearance of physical facilities, equipment, personnel and communication materials; reliability—ability to perform the promised service safely and correctly; responsiveness—willingness to help clients and provide prompt service; assurance—knowledge and courtesy of employees and their ability to inspire trust and empathy—personalized attention given to customers) [25]. A total of 100 points is allocated among the five dimensions.

As secondary outcomes, we define the gap between users' perception and expectations, each partial assessment for five different domains included in the SERVQUAL questionnaire, and finally, the overall participants' perception of the service.

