A model previously proposed was used to detect the gap between users' perceptions and expectations [26]. For that, the SERVQUAL questionnaire was applied in two different moments (before and after receiving care). Then, the difference between the scores that customers attribute to the different pairs of statements. After consent to participate in the study, the baseline questionnaire will be sent to participants when contacted to participate in the study. This baseline assessment (t-2) should be done two weeks before the allocation (t0). We will calculate the mean score attributed in the baseline SERVQUAL assessment (t2) in each dimension to evaluate individual dimensions separately. Finally, one extra item was included besides the mentioned questionnaire (t2): "How do you feel about these service attributes that are already provided?". It was scored on a 5-point Likert-type scale of "very bad (1)" to "very good (5)." to identify overall participants' perceptions.

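### The primary RCT test is left to the observed score distribution, and the stratification factors and pre-allocation SERVQUAL score are not built into it; one prespecified adjusted linear model would fix the effect measure and gain precision at no cost

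*Protocol article*

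**What the plan says.** The RCT's primary outcome is the caregiver's SERVQUAL perception score two weeks after the intervention, or after two weeks of waiting (RCT, Outcomes). The analysis section states: "This study will first compare the satisfaction with the health care received using the SERVQUAL score between the groups". It continues: "We will use an appropriate statistical test depending on the distribution of scores". No test, decision rule or effect measure is named. Covariates appear only as an addition: "Appropriate regression analyses may also be performed to verify other variables' influence, besides the group (test vs control". A further comparison follows: "We will also compare the gaps (difference between expected and perceived) between groups". For this too, the approach is to be chosen after the distributions are checked.

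Two design features bear on this. On randomisation (RCT, Interventions): "The stratification will be performed considering the dentist will provide the non-face-to-face consultation and the week for inclusion". The stated result is: "In this way, balanced randomization was obtained per professional each week". On baseline (RCT, Outcomes), SERVQUAL is completed at t-2, two weeks before allocation, and provides the expectation side of the gap, which is a secondary outcome. That section then describes the dimension scores as follows: "We will calculate the mean score attributed in the baseline SERVQUAL assessment (t2) in each dimension". Elsewhere t2 is the outcome time.

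The sample size section assumes a difference of 0.17 and an SD of 0.53. It gives a minimum of 306 and, with 20% added, 368 families.

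**The concern.** There are two separate points.

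**What is estimated.** The trial is sized on a difference in means. A t-test addresses that quantity; a rank test does not. If the shape of the scores decides the test, it also decides the effect measure. The article's later steps need means: the simulation study seeks mean values with 95% confidence intervals for user satisfaction, and the economic analysis defines effect as a difference between strategies.

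**Information left out.** Balancing the arms within dentist and week removes that source of variation from the true sampling error of the group difference. An analysis that omits the strata still counts it in the standard error. A SERVQUAL score taken before allocation is likewise available to reduce residual variance, but it is assigned only to the secondary gap comparison. What is at stake is precision and a fixed estimand, not validity.

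**Working it through.** **1. The plan's own figure.** Inputs from RCT, Sample size: difference 0.17, SD 0.53. Alpha, sidedness, power and allocation ratio are not given as numbers; two-sided 5%, 80% and 1:1 are assumed.

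n per arm = 2 × (1.960 + 0.842)² × 0.53² / 0.17² = 152.6, rounded up to 153, so 306 in total. This matches. 306 × 1.2 = 367.2, stated as 368. Other conventions do not give 306: one-sided 80% gives 242, two-sided 85% gives 350 and two-sided 90% gives 410. The sizing is therefore that of a plain unadjusted comparison of two means.

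SE at 153 per arm = 0.53 × √(2/153) = 0.0606. Power = Φ(0.17/0.0606 − 1.96) = Φ(0.845) = 80.1%.

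**2. Adding the t-2 score.** With correlation r between t-2 and t2 scores, the SE is multiplied by √(1 − r²). Power = Φ(0.17 / (0.0606 × √(1 − r²)) − 1.96). The values of r are assumptions.

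| r | variance kept | SE | power at 306 | total N for 80% | 95% CI half-width |
|---|---|---|---|---|---|
| 0 | 1.00 | 0.0606 | 80.1% | 306 | 0.119 |
| 0.2 | 0.96 | 0.0594 | 81.7% | 294 | 0.116 |
| 0.3 | 0.91 | 0.0578 | 83.7% | 278 | 0.113 |
| 0.4 | 0.84 | 0.0555 | 86.5% | 258 | 0.109 |
| 0.5 | 0.75 | 0.0525 | 90.0% | 230 | 0.103 |

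**3. Leaving out the strata.** Let v be the share of outcome variance explained by dentist and week, equal in both arms (assumed). The unadjusted SE is too large by 1/√(1 − v) − 1, so the actual two-sided type I error is 2Φ(−1.96/√(1 − v)):

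- v = 5%: SE 2.6% too large, type I error 4.4%
- v = 10%: SE 5.4% too large, type I error 3.9%
- v = 20%: SE 11.8% too large, type I error 2.8%

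A simulation with 78 assumed strata of 4 (312 families, 4,000 runs) gave 4.5%, 3.4% and 3.2% for the unadjusted t-test. The Monte Carlo standard error is √(0.05 × 0.95/4000) = 0.3 points. Power was 82%, 83% and 84% unadjusted against 84%, 86% and 88% with strata in the model. The error is on the conservative side throughout.

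**4. Choosing the test from the data.** Simulated type I error at 153 per arm, for normal scores and for scores with a ceiling:

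- a fixed rule (Shapiro–Wilk, then t-test or Mann–Whitney): 5.0% and 5.2%
- always taking the smaller of the two p-values: 6.0% and 5.8%

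The main cost of the open choice is therefore the change of estimand.

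**5. The gap.** If the gap is the t2 score minus the t-2 score, regressing it on group and t-2 score gives the same group coefficient as regressing the t2 score on group and t-2 score. Only the t-2 coefficient shifts, by 1. With the gap defined the other way round, the group coefficient changes sign only. One model therefore serves both between-group comparisons.

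**The case against.** The strongest reply is that the article does not call the analysis unadjusted. Regression is allowed, and the section on independent variables lists covariates for both trials. Naming model covariates is commonly left to a statistical analysis plan, which is not shown. This stands in part: the missing covariate names would not be a finding on their own. But the article does affirmatively fix a test that depends on the scores, and it places regression after that test as an option for examining other variables' influence.

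The size of the gain is also open. The t-2 questionnaire measures expectations and the t2 questionnaire perceptions, so r may be low; at r = 0.2 the gain is 1.6 points. Before t2 the waiting-list arm has had no teleconsultation, so a dentist effect through that consultation can arise only in the intervention arm, although dentists' previous face-to-face care could matter in both. Both points stand.

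A reader might infer more than the documents support:

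- **That the analysis choice leaves the trial underpowered.** Power falls to about 78% only if 294 families (368 less 20%) are analysed. That concerns the loss allowance, not the test. At the plan's 306 the unadjusted comparison has 80.1%, and imputation under intention to treat is foreseen.
- **That false positives are inflated.** Omitting the strata is conservative, and a fixed selection rule holds about 5%.
- **That the raw gap comparison has a known, lower power.** This would need 0.53 to be the SD of a score, with equal SDs at both times. The article derives 0.17 from a perceived-minus-expected difference and does not settle what 0.53 describes.
- **That dimension outcomes come from pre-randomisation data.** The same Outcomes paragraph and the Interventions section label baseline t-2, and the analysis section compares perception by dimension. The label is a slip.

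**Conclusion.** The point holds as a free improvement, not as an error that invalidates the trial. The primary test should not depend on the observed distribution, because a rank test would not estimate the mean difference of 0.17 used for sizing. Omitting strata and baseline costs precision.

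For baseline, adjustment adds 1.6 to 9.9 points of power at 306 families over r = 0.2 to 0.5. For strata, the simulated gain from adjustment is about 3 to 4.5 points when they carry 10 to 20% of the variance. Both gains vanish if r and the strata's share are zero. Neither quantity is in the documents, and the ranges are assumptions, as are two-sided 5%, 80% power and 1:1 allocation. The implied planned power is met without adjustment. The time label is a clerical matter that the surrounding text resolves.

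**What to change.** In the RCT analysis section, replace the sentence on choosing a test with a named primary analysis: a linear model of the t2 SERVQUAL score on group, t-2 SERVQUAL score, dentist and inclusion week, with week grouped or entered as a random effect if strata are sparse. Use robust standard errors and report the adjusted mean difference with 95% CI. Keep a rank-based test as a sensitivity analysis only. Use the same model for each dimension score, with that dimension's t-2 score as covariate, and for the between-group gap comparison.

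In RCT, Outcomes, label the baseline assessment t-2 and state that dimension perception scores come from t2.

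The cost is wording only. Dentist, week and t-2 SERVQUAL are already part of the design, so no new data or extra families are needed. The change should be dated and fixed before outcome data are compared by group.
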